## 2. Materials and Methods

### 2.1. Design

A parallel-group randomised controlled trial will be conducted including a 3-month intervention phase, followed by 1-month follow-up. Participants will be randomly assigned to the experimental or control group. For both groups (control and experimental), assessments will be carried out at baseline (before starting the intervention), right after finishing the intervention and an additional follow-up assessment 1 month after the end of the programme. The study will be conducted following the *Consolidated Standards of Reporting Trials Statement* (CONSORT) [26].

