### 2.3. Sample Size

Sample size computations were conducted by using G*Power software 3.1.9.4 (Kiel University, Kiel, Germany) and selecting the statistical test to compare the difference between two independent means (two groups). Thus, accepting a 0.05 alpha risk and a 0.2 beta risk in a bilateral contrast and assuming a moderate effect size of 0.5 [27], a total of 128 participants (64 subjects in the experimental group and 64 in the control group) were sufficient for achieving a minimum power of 80%. 

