### 2.8. Statistical Analysis

Descriptive statistics and computations will be performed with SPSS (version 25.0; IBM SPSS Inc., Armonk, IL, USA). Data will be presented as means and standard deviation (SD).

The normality and homogeneity of data will be checked applying Kolmogorov–Smirnov and Levene’s test, respectively. Then, a repeated measures ANCOVA will be applied to analyse the intervention effects on the different dependent variables, adjusted by age and baseline outcomes. Cohen’s d (with 95% confidence interval) will be also included in the results as the effect size. Effect sizes thresholds will be interpreted as follow: >0.2, small; >0.5, moderate; >0.8, large [27]. Statistical significance will be computed for the effect of time and the interaction group × time. Alpha level will be fixed at *p* ≤ 0.05.

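### Section 2.8 adjusts for baseline but names only time and group × time as tests, without stating the levels of time; on the ordinary reading no named test addresses a sustained intervention effect

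*Protocol article*

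**What the plan says.** Section 2.1 schedules three assessments in both groups: "assessments will be carried out at baseline (before starting the intervention), right after finishing the intervention and an additional follow-up assessment 1 month after" the programme ends. Section 2.8 says that "a repeated measures ANCOVA will be applied to analyse the intervention effects on the different dependent variables, adjusted by age and baseline outcomes". It then lists what will be tested: "Statistical significance will be computed for the effect of time and the interaction group × time". The threshold follows: "Alpha level will be fixed at *p* ≤ 0.05". Cohen's d with a 95% confidence interval is promised as the effect size, but the contrast that it measures is not defined. The section does not state the levels of the time factor, and it names neither a group main effect nor a between-group contrast at any visit.

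Section 2.3 bases the sample size on a comparison of two independent means, "accepting a 0.05 alpha risk and a 0.2 beta risk in a bilateral contrast" and "assuming a moderate effect size of 0.5", which gives 64 children per group.

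**The concern.** The outcome is measured three times. If the baseline value is a covariate, the usual consequence is that it is no longer an outcome, and the repeated factor has two levels left: end of intervention and follow-up. In that model the intervention effect is the adjusted difference between groups, either at each visit or averaged over both. Group × time is a different quantity, namely the effect at follow-up minus the effect at the end of the intervention. It shows whether the effect persists. It does not show whether there is one.

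The second named test, the effect of time, pools both arms and does not compare them. On this reading neither named test addresses the study's aim of evaluating the programme's effectiveness. A programme that works and keeps its effect would usually give a non-significant group × time test. One whose effect disappears within a month would usually give a significant one. The comparison for which the trial is powered would have no place in the list of tests.

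**Working it through.** **Inputs from the protocol article.** 64 per arm, 1:1, d = 0.5, two-sided alpha 0.05, power 80% (Section 2.3); one baseline and two later visits (Section 2.1); covariates age and baseline outcome (Section 2.8).

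**Assumed, because the article gives no figure.** Between-visit correlation r, equal for all pairs of visits, from 0.3 to 0.8; SD 1 at every visit; normal, independent, complete data.

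**Step 1: the plan's own figure.** The normal approximation gives n per arm = 2 × (1.960 + 0.842)² / 0.5² = 62.8, so 63. The exact noncentral t calculation gives 63.77, so 64 per arm and 128 in total, with power 80.1%. The stated sample size reproduces. It is the size for a between-group difference.

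**Step 2: what group × time estimates when time has two levels.** Let D1 be the group difference at the end of the intervention and D2 the difference at follow-up. Then group × time estimates D2 − D1.

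- Sustained benefit: 0.5 − 0.5 = 0, so the rejection rate equals alpha whatever the correlation.
- Benefit halved at follow-up: 0.25 − 0.5 = −0.25.
- Benefit gone at follow-up: 0 − 0.5 = −0.5.

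**Step 3: closed-form check at r = 0.5.**

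- Group contrast at the end of the intervention, adjusted for baseline: residual variance 1 − r² = 0.75; SE = √(2 × 0.75 / 64) = 0.153; 0.5 / 0.153 = 3.27; power ≈ Φ(3.27 − 1.96) ≈ 0.90.
- Group × time when the benefit is gone at follow-up: variance of the within-child difference 2(1 − r) = 1; SE = √(2 × 1 / 64) = 0.177; 0.5 / 0.177 = 2.83; power ≈ Φ(2.83 − 1.96) ≈ 0.81.

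Both agree with the simulation below (0.891 and 0.810).

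**Step 4: simulation.** 3,000 trials per scenario, age and baseline as covariates. The Monte Carlo standard error at 5% is √(0.05 × 0.95 / 3000) ≈ 0.4 percentage points.

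| True effect (end, follow-up) | Test | r = 0.3 | r = 0.5 | r = 0.7 | r = 0.8 |
|---|---|---|---|---|---|
| 0.5, 0.5 | Group × time, two levels | 5.2% | 4.6% | 5.2% | 5.4% |
| 0.5, 0.5 | Adjusted group contrast at end | 82.7% | 89.1% | 97.0% | 99.7% |
| 0.5, 0.5 | Adjusted group main effect | 96.2% | 97.5% | 99.6% | >99.9% |
| 0.5, 0.25 | Group × time, two levels | 22.8% | 28.7% | 43.0% | 59.3% |
| 0.5, 0 | Group × time, two levels | 65.3% | 81.0% | 94.9% | 99.2% |

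**Step 5: the other reading, with baseline as a level of time.** For the sustained 0.5 SD effect, the univariate group × time test over three levels rejects in 69% to >99% of trials without the baseline covariate, and in 86% to 100% with it. With no effect, the version with the covariate rejects in 4.4% to 5.4%.

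The redundancy does little harm for an algebraic reason. With baseline B among the regressors, regressing (end − B) or end alone on group, age and B gives the same group coefficient and the same residuals. The same holds at follow-up. The multivariate group × time test is therefore the joint test of the two baseline-adjusted group differences. In a separate simulation the two tests coincided in every run, with power of 93% to >99% for the sustained effect.

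**The case against.** The strongest reply is that Section 2.8 never says that time has two levels. Three assessments are scheduled, and time plus group × time is the customary wording for a three-occasion design in which the interaction carries the treatment effect. The model is also introduced as the analysis of intervention effects. On that reading, Step 5 shows that the test works. This stands, and it makes the harm conditional.

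A reader might infer from the text that baseline on both sides of the model invalidates the analysis. It does not: the specification is redundant, but its multivariate test is valid and the univariate version holds its error rate in the simulation. That an omnibus test does not show at which visit the effect lies is no finding either, since follow-up contrasts are commonly left to an analysis plan.

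A reader might also infer that the trial will report the opposite of what its data show. The article does not support that. The levels of time are open, and the promised interval for Cohen's d would display a sustained difference if d is computed between groups. Nor does Section 2.8 offer the time effect as proof of benefit; it says only that its significance will be computed.

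Two parts of the reply do not remove the point. Cohen's d has no defined contrast and is given as an effect size beside the named tests. And the choice of tests was not deferred to an analysis plan: the article fixes it, so a plan that follows the article inherits the problem.

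**Conclusion.** The point holds in conditional form. Section 2.8 leaves the levels of time unstated, and on the ordinary reading of a model adjusted for baseline its named interaction is the wrong test of effectiveness. For a sustained 0.5 SD benefit, the effect size assumed in Section 2.3, that test has about 5% power, against about 83% to 99.7% for the adjusted contrast at the end of the intervention. The 5% follows from algebra and does not depend on the correlation. The other figures rest on the assumed correlations of 0.3 to 0.8, equal variances and complete, independent data.

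If baseline is also a level of time, the named test is essentially sound and only the redundancy needs tidying. The sample size arithmetic is correct; what is missing is a named test that clearly corresponds to it.

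**What to change.** State the levels of time in Section 2.8 and name the test of the intervention effect. Either of two forms will do, and one should be fixed before group data are examined.

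- **Baseline as covariate.** Time has two levels, end of intervention and 1-month follow-up. The intervention effect is the between-group difference adjusted for baseline and age, at the end of the intervention and at follow-up, with 95% CI, or alternatively the group main effect over both visits. Group × time is reported only to assess persistence. The two choices differ if the benefit fades: with an effect of 0.5 SD at the end and none at follow-up, the main effect has power of 47% to 78% for r = 0.3 to 0.8, while the contrast at the end of the intervention keeps about 83% to 99.8%.
- **Baseline as a level of time.** Time has three levels, baseline is dropped as a covariate, and group × time is the test. For a sustained effect this has less power at low correlation (69% at r = 0.3, 83% at r = 0.5).

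The contrast behind Cohen's d should be defined to match. The cost is a few sentences: visits, data and sample size stay as they are.

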## 3. Discussion

A great interest in the concept of PL is emerging due to its comprehensive character on the development of physical activity. Several studies have started to evaluate and design intervention programmes based on it [30,31,44,45]. However, most of them are focused on some of the domains that comprised PL and not overall. Moreover, most programmes have been carried out within physical education classes [44,45] or in out-of-school settings [30,31]. This project would be the first to implement a programme to develop PL during the break period of the school day and, to the best of our knowledge, the first in Portugal to assess PL in children. 

In Portugal, around 35% of Portuguese people over 14 years old never or rarely take active breaks (e.g., walking, standing or jogging) during sitting time [6]. Break times may be an ideal time for the development of PL, as it has been shown that education and health interventions can improve the physical fitness and health of their participants [22]. In addition, this intervention would contribute towards meeting the World Health Organisation’s physical activity recommendations, which state that children aged 5–17 years should engage in at least 60 min of Moderate to Vigorous Physical Activity (MVPA) per day [46]. It has also been shown that the daily steps taken by students participating in an active school break can be increased compared to those who do not [47,48]. This would help fulfil the daily recommendations set out by the President’s Council on Physical Fitness and Sports, recommending 12,000 steps for girls and 15,000 steps for boys [49]. 

All these benefits have recently led to the development of numerous research studies, which implemented active breaks programmes with different objectives based on different activities, such as alternative, popular and traditional games [47]; free play [50]; pre-sports games [51]; and high-intensity interval training (HIIT) [52] o HIIT + intermittent training [53]. However, any previous study has aimed to develop PL into the school context.

Regarding level of PL, several studies have provided results in schoolchildren from different countries [54,55,56,57,58] based on CAPL-2. Most reported worrying results since more than 50% of the schoolchildren participating in these studies did not achieve sufficient PL [54,55,56,58]. 

More specifically, concerning the “daily activity” domain, which is one of the most relevant due to the consideration of sedentary behaviour as a disease of the 21st century [8,9], previous studies using CAPL-2, observed that the majority of schoolchildren (more than 50%) are in the “insufficient” or “in progress” categories [54,55,56,57]. These results are in line with IAN-AF 2015–2016 outcomes [6], which stated that children and adolescents aged 6–14 years spend on average 9 h and 6 min daily in sedentary behaviours (excluding sleep time) [6]. Moreover, the average time spent in these behaviours increases significantly with age, proceeding from around 8 h in the youngest group and close to 10 h in adolescents [6]. This highlights the importance of promoting active habits at school age, as physical inactivity during the first years of life is considered a relevant factor in the increase in obesity levels and other serious medical disorders in children and adolescents [59].

A previous study has shown that “motivation and confidence” and “physical competence” domains are the CAPL domains with the strongest correlation [60]. Specifically, recent studies found that the greater the percentage of schoolchildren in the domain “motivation and confidence”, the greater the percentage for “physical competence” [57,58]. Other studies have shown that physically active students scored higher on autonomous motivation than non-active students [61,62] and that students who satisfied the needs for autonomy, competence and relatedness were more likely to participate in PE-related activities for self-determined reasons and were less likely to feel demotivated [61]. This highlights the role that motivation plays in the practice and possible adherence to physical activity and, hence, the importance of its assessment in being able to detect possible deficits and, as a consequence, redirect intervention strategies.

Regarding the “knowledge and understanding” domain, previous studies showed that most of the schoolchildren were “in progress” or were “insufficient” [55,56,63]. In this sense, there are hardly any studies that evaluate how knowledge of PA affects subsequent practice. In contrast, other studies that have evaluated how knowledge of certain pathologies affects subsequent treatment have obtained beneficial results [64,65]. Therefore, due to the worrying results reported by the different studies on low knowledge and understanding in this field [54,55,56,58], this study could be very beneficial as an increase in the knowledge about PA could translate into an increase in PL since a relationship has also been found between the two [60]. 

Body composition can have a considerable influence on PL, as several studies have reported significant differences between overweight and non-overweight schoolchildren for the different domains that make up PL [66,67,68,69,70,71,72]. Specifically, in the “daily activity” domain, it has been observed that schoolchildren with obesity performed less daily activity related to physical activity than schoolchildren without obesity [66]. For “physical competence”, it has been shown that overweight schoolchildren have worsened physical competence compared to their normal-weight counterparts [67,68,69,70,71]. In the same line, motivation towards physical activity has been found to be lower in overweight schoolchildren [72]. Regarding the level of knowledge about physical activity, few studies have evaluated this factor in isolation among overweight and obese schoolchildren. However, Nyström, Traversy, Barnes, Chaput, Longmuir and Tremblay [60] reported differences, showing higher knowledge in non-overweight boys. 

Regarding PL and body composition, previous studies have reported a negative correlation between PL and BMI, fat mass [20,58], HRQoL and blood pressure [20]. Nyström, Traversy, Barnes, Chaput, Longmuir and Tremblay [60] and Mendoza-Muñoz, Barrios-Fernández, Adsuar, Pastor-Cisneros, Risco-Gil, García-Gordillo and Carlos-Vivas [58] found that children with a healthy weight scored significantly better on the CAPL than overweight children. Therefore, it can be hypothesised that the development of PL could translate into improved body composition values.

Therefore, the development of educational programmes that promote both knowledges in the field of physical education and the promotion of active and healthy lifestyle habits, as well as considering motivation in the development of these habits, could favour a complete development of PL. This is not limited to the mere development of physical fitness but also of individual fitness. The positioning of PL as a determinant of health is not a novel idea, but little attention has been paid to what this means and its implications [73]. In Portugal, there are no studies in which PL in children is being assessed nor programmes that aim to develop it. However, we consider this model of assessment and multidimensional work to be of great interest, so this study aims to be a starting point to stimulate empirical research on PL. This intervention program will allow children to participate in structured and full physical activity. Interestingly, given that the emphasis of PL is on maximising individual attributes, everyone can achieve it regardless of the initial skill set or level of physical fitness [74]. 

In this sense, the intention of PL proceeds beyond simply being able to define or explain the concept of healthy living but also involves enabling an individual to actualise their inherent potential to adopt and develop a healthy lifestyle [75]. The entrenchment of PL in the educational system would allow the consolidation of a unifying term (and similar to other educational subjects) to describe the overall outcome of quality physical education, physical activity, sport and recreation programmes. Therefore, PL could provide a basis for sport, public health and physical education, which involves trying to promote PL in all areas and addressing it from the early childhood stage so that physical activity can be enjoyed and adhered to from an early age.

One of the main strengths of this study is that the assessment uses CAPL. This instrument is one technique that is most closely aligned to the concept of a child’s PL, as it assesses daily activity, motivation and confidence, knowledge and understanding and physical competence. In addition, it has been shown to be a valid and reliable instrument in school children and, recently, in adolescents. Furthermore, in the last year, it has started to be used in countries such as Denmark [63], Greece [55] and China [56], which will allow for future comparisons between different countries.

The present study does not report preliminary data; this study only reports the study protocol that will be performed in the future. This can be considered as a limitation of the study. As future research lines, we propose the evaluation of PL in adolescent individuals and monitoring its evolution from childhood to this stage. Moreover, it will also be interesting to analyse the differences in the level of PL between stages and to identify relationships between PL domains and health-related outcomes. This would allow the detection of deficiencies and guide interventions to prevent diseases such as obesity.

## 4. Conclusions

The present study will investigate the efficacy of PLBreaks in schoolchildren to improve their PL and body composition. If the efficacy of the program is demonstrated, it can be implemented in schools.

Therefore, the main added value of this study is the acquisition of new knowledge concerning PL from an immediate perspective of practical and direct application. It will represent a scientific advance in terms of improvement and adherence to health-related PA, as well as the prevention of diseases associated with physical inactivity such as overweight and obesity.

On the other hand, the PLBreaks could be the response for solutions to a social problem such as the difficulties of access in many cases (due to socio-economic reasons) to PA programmes that are related to health. Thus, given that it is a low-cost programme that can be easily standardised by levels of difficulty (adapting to the different levels of PA), its transfer and implementation would not be a problem in the public sphere, and it includes the possibility of including the intervention in public education programmes.

## Data Availability

Not applicable.
